# Study title

Effect of indomethacin on the progression of Alzheimer’s disease. A randomized double blind, placebo-controlled, multicenter clinical trial.

# Introduction

Inflammatory mechanisms are supposed to play an important role in the neuronal degeneration in patients with Alzheimer’s disease. This degeneration is associated with extracellular deposits of amyloid- protein (A) in senile plaques, abnormal phosphorylation of intraneuronal tau-proteins (neurofibrillary tangles) and clusters of activated microglial cells associated with senile plaques1;2.

Currently, international interest is directed to the role of activated microglial cells and their production of cytokines2-4. The acute phase protein 1-antichymotrypsin (1-ACT), various complement factors (e.g. C1q), the intercellular adhesion molecule-1 (ICAM-1) and the cytokine interleukin-6 (IL-6) can be detected in senile plaques5-8. Increased activity of 1-ACT9-12 and decreased concentrations of IL-6 and C1q13;14 were found in cerebrospinal fluid of patients with Alzheimer’s disease. Presumably, activation of microglial cells occurs through interaction of A proteins with microglial cells, mediated by a “receptor for advanced glycosylation end-products”(RAGE)15.

It is hypothesized that cytokines produced by activated microglial cells damage neurons and thus contribute to the deterioration of patients with Alzheimer’s disease. In this way, inhibition of production of cytokines would prevent the progression of the disease.

In retrospective epidemiological research the number of patients having arthritis and Alzheimer’s disease at the same time, was lower than to be expected from prevalence numbers of Alzheimer’s disease16. Presumably the use of nonsteroid anti-inflammatory drugs (NSAIDs) can account for this effect. Also, a twin study confirmed the decreased risk of Alzheimer’s disease when using NSAIDs17. A recent review of 17 epidemiological studies showed a consistent relation between the use of NSAIDs and a decreased incidence of Alzheimer’s disease18.

Based on these results a double blind, placebo-controlled trial was conducted with indomethacin in 44 patients with Alzheimer’s disease19. They concluded that patients in the indomethacin group deteriorated less rapidly than patients in the placebo group. However, because of the small number of patients studied, this trial should be reproduced.

The prospect of retarding the progression of Alzheimer’s disease with easily available and inexpensive drugs like NSAIDs is very attractive. Unfortunately, treatment with NSAIDs in the elderly is hampered by their toxicity and related serious side effects, including gastrointestinal bleeding and ulcers.

# Study objectives

## Primary objective

To assess whether indomethacin is able to retard disease progression in mild to moderate Alzheimer’s disease.

## Secondary objectives

- To evaluate the effect of indomethacin compared to placebo on cognitive and behavioral dysfunction and dysfunction in the activities of daily living in patients with mild to moderate Alzheimer’s disease.
- To evaluate the safety and tolerability of indomethacin.

# Study design

A randomized double blind, placebo-controlled, multicenter clinical trial to evaluate the effect of indomethacin over a one year period on the progression of mild to moderate Alzheimer’s disease. Following screening and baseline assessments, 160 patients will either receive indomethacin or placebo.

Evaluation of the ability of indomethacin to retard disease progression will be performed in weeks 26 and 52 (ADAS-cog/non-cog, MMSE, CIBIC+, NPI and IDDD). Safety en tolerability evaluations will be performed in weeks 4, 8, 26 and 52 (adverse events, physical examination, vital signs and laboratory evaluations). The evaluation schedule is specified in Appendix III.

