# Duration

## Patients

The study duration for the patient, from baseline to final evaluation, is one year. Six visits will take place in which different evaluations will be conducted. The evaluation schedule is specified in Appendix II.

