## Secondary outcome measures

Noncognitive subscale of the Alzheimer’s Disease Assessment Scale (ADAS-noncog): The noncognitive subscale evaluates the severity of noncognitive behavioral dysfunction. It consists of 10 items and a maximum score of 50 points.

Clinician Interview-Based Impression of Change with caregiver input (CIBIC+): The CIBIC+ is a global assessment instrument intended to provide an index of *clinically* important change that cannot be obtained from quantitative assessment measures such as mental status examinations (range 1 to 7)23.

Mini-Mental State Examination (MMSE): The MMSE is the most widely used screening instrument in Alzheimer’s disease drug studies. It is a short assessment, evaluating memory, attention, concentration, naming, repetition, comprehension, and the capacity to create a sentence. The MMSE is also frequently used to stratify patients according to disease severity. A perfect score on the MMSE is 30 and is influenced by educational achievement.

Neuropsychiatric Inventory (NPI): The NPI was developed to assess the severity and frequency of psychopathology (12 items) in dementia patients. The NPI-D assesses the amount of caregiver distress engendered by each of the neuropsychiatric disorders.24

The Interview for Deterioration in Daily living activities in Dementia (IDDD): The IDDD is a caregiver-based measure, which consists of 20 concretely worded items, reflecting the initiative to perform and actual performance of self-care and more complex activities.25

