## Statistical methods

In the final analysis of the results a so-called “evaluation of increment” will take place. Change in ADAS-cog score (primary outcome measure) of every patient will be compared between two groups by means of a 2 x 2 ANOVA (categories: group, time;  = 0.05).

Secondary outcome measures will be analyzed following the same procedure, with correction for multiple equations.

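### The IDDD is timed at weeks 26 and 52 in section 4 but is blank at every visit in Appendix II, and no baseline IDDD is explicitly scheduled

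*Protocol*

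**What the plan says.** - Section 3.2 (Secondary objectives) includes the effect of indomethacin on "cognitive and behavioral dysfunction and dysfunction in the activities of daily living".
- Section 10.2 (Secondary outcome measures) lists five instruments: ADAS-noncog, CIBIC+, MMSE, NPI and IDDD. Of the last it says: "The IDDD is a caregiver-based measure, which consists of 20 concretely worded items". It is the only one of the five described as measuring daily activities.
- Section 4 (Study design) states that evaluation of disease progression "will be performed in weeks 26 and 52 (ADAS-cog/non-cog, MMSE, CIBIC+, NPI and IDDD").
- Appendix II (Evaluation Schedule) has a row for the IDDD with no mark in any of its seven visit columns.
- Section 12.3 (Statistical methods) says of the primary outcome: "Change in ADAS-cog score (primary outcome measure) of every patient will be compared between two groups". For the others: "Secondary outcome measures will be analyzed following the same procedure".
- On where the schedule is found, section 4 says "The evaluation schedule is specified in Appendix III", while section 6.1 (Patients) says "The evaluation schedule is specified in Appendix II". The table itself is headed Appendix II.

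**The concern.** The body text and the visit table give different instructions for the same instrument, and both cannot be followed. The table is the natural working document for staff at a visit. The trial is multicenter, recruits through several clinics (section 5.5) and allows later assessments at the patient's home (section 15.2), so some staff may rely on the table alone.

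At stake is the one scale dedicated to daily living, which is a named element of the secondary objective. The baseline matters most. The planned analysis compares change, and a pre-treatment IDDD that was not taken cannot be obtained afterwards. No analysis plan can repair that.

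**Working it through.** No figure in the protocol needs to be reproduced here. The check is a comparison of passages and a count of table cells.

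**Step 1: section 4 against Appendix II.** The table has seven visit columns: screening, baseline, and weeks 4, 8, 26, 38 and 52.

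| Instrument | Section 4 | Marked in Appendix II | Cells marked |
| --- | --- | --- | --- |
| ADAS-cog | weeks 26, 52 | baseline, 26, 52 | 3 of 7 |
| ADAS-noncog | weeks 26, 52 | baseline, 26, 52 | 3 of 7 |
| MMSE | weeks 26, 52 | screening, baseline, 26, 52 | 4 of 7 |
| CIBIC+ | weeks 26, 52 | baseline, 26, 52 | 3 of 7 |
| NPI | weeks 26, 52 | baseline, 26, 52 | 3 of 7 |
| IDDD | weeks 26, 52 | none | 0 of 7 |

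For five of the six instruments the two places agree on weeks 26 and 52, and the table supplies the baseline. The IDDD is the exception, and its row is the only one in the whole table without a mark.

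**Step 2: what the analysis needs.** Section 12.3 applies the primary outcome's change-score procedure to the secondary outcomes. Section 12.1 (Sample size) speaks of changes from baseline. The IDDD therefore needs a baseline and at least one follow-up value.

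**Step 3: what each reading yields per patient.**
- Appendix II as printed: 0 IDDD observations.
- The timing sentence in section 4: 2 follow-up observations, with the baseline left to inference.

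**Step 4: size.** Inputs are 160 patients (sections 4 and 5.1) and two follow-up times (section 4).
- Explicitly planned follow-up assessments: 160 x 2 = 320.
- Baselines implied by the change analysis: 160 x 1 = 160.
- Ceiling: 320 + 160 = 480.

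Section 12.1 assumes 20 percent dropout without saying when it occurs. If, as an assumption, all of it fell before week 26, the follow-up count would be 160 x 0.80 x 2 = 256. The range is then 256 to 320 follow-ups, and 416 to 480 with the baselines.

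**Step 5: the cross-reference.** Section 4 points to Appendix III for the schedule. Section 7.4 (Informed consent) cites Appendix III for consent material. Section 6.1 and the heading of the table both say Appendix II, so the reference in section 4 is wrong.

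**The case against.** The best case for the plan is that its intent is clear. The IDDD is described as a secondary outcome, timed in the design section and given its own row in the table. A row that exists but is empty looks like a slip, and a careful user would notice it. Section 4 is as much part of the protocol as the appendix, so data are lost only if the table is followed over the text. That the table would prevail is an assumption: the protocol does not say so, and the case report forms are not shown. All of this stands, and it limits the weight of the point.

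A reader might infer that section 4 has a second defect because it names no baseline IDDD. The document does not support that. The timing sentence names no baseline for any scale, the ADAS-cog included, and the sentence before it refers generally to baseline assessments. The gap is particular to the IDDD only because its row in Appendix II, where the other scales get their baseline mark, is blank.

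The marks could also have been lost when the table was read from the file. This cannot be excluded entirely. But the row keeps all seven cells, and the rows directly above and below keep their marks, so nothing points that way.

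The objections do not remove the contradiction itself, nor the fact that nothing in the protocol explicitly schedules a baseline IDDD.

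**Conclusion.** The point holds as an internal inconsistency that is wrong as written and should be fixed. Section 4 and Appendix II contradict each other on the IDDD at weeks 26 and 52, and the baseline that section 12.3 requires is only implied. If the table is followed, the trial has no data from its only dedicated daily-living scale.

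A reader might go further and conclude that the daily-living objective cannot be answered, or that the IDDD has been dropped. Neither follows. Section 4 does time the two follow-up assessments, so the loss depends on the table being followed instead. Daily living is also one element of a single secondary objective that covers cognition and behavior as well.

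The size is at most 320 stated follow-up assessments plus 160 implied baselines, before dropout. The 480 total is a ceiling that assumes all 160 patients, three assessments each and strict adherence to the printed table. The primary ADAS-cog outcome, its schedule and the sample size are not affected, so this does not rank among the errors that threaten the trial's main conclusion. It still deserves correction before enrolment, because a missed baseline is irreversible.

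**What to change.** In Appendix II, mark the IDDD at baseline, week 26 and week 52, as for the NPI and CIBIC+. In section 4, change the reference for the evaluation schedule from Appendix III to Appendix II.

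The cost is a correction to one table row and one cross-reference. These visits already take place, so the only fieldwork is a 20-item caregiver interview at each of three visits. At weeks 26 and 52 section 4 already calls for it.

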# Patient selection

## Number of patients and target population

Approximately 160 patients with mild to moderate Alzheimer’s disease who satisfy inclusion and exclusion criteria will enter the study. Patients will be randomly assigned to either the medication or the placebo group (80 patients per group).

## Inclusion criteria

- The patient will satisfy the DSM-IV criteria for dementia of the Alzheimer’s type.
- The patient will satisfy the NINCDS/ADRDA criteria for the clinical diagnosis of probable Alzheimer’s disease (Appendix I)20.
- The severity of dementia for each patient will be quantified by a Mini-Mental State Examination (MMSE) score between 10 and 26 (both inclusive).
- The patient is living at home or in a home for the elderly.
- The patient has a responsible caregiver who is able to provide information about the patient’s functional status.
- Written informed consent is obtained from the patient or the legally accepted representative.

## Exclusion criteria

- The patient satisfies the NINDS-AIREN criteria for probable vascular dementia, including:
- presence of focal signs on neurological examination consistent with stroke
- evidence of relevant cerebrovascular disease by brain imaging (CT and/or MRI made within two years before the baseline visit)
- A known exaggerated pharmacological sensitivity or allergy to NSAID’s.
- History of peptic ulceration, gastric surgery or gastrointestinal bleeding.
- Current diagnosis of active peptic ulceration.
- Current diagnosis of severe and unstable cardiovascular disease.
- Current diagnosis of renal failure (creatinin > 200 mol/l).
- Advanced, severe and unstable disease of any type, other than Alzheimer’s disease, that may interfere with primary and secondary variable evaluations, including a medical condition which should be expected to progress, recur, or change to such an extent that it may bias the assessment of the clinical or mental status of the patient to a significant degree or put the patient at special risk.
- Intake of any of the following concomitant medications:
- salicylates
- coumarin derivatives
- ACE-inhibitors
- loopdiuretics
- Intake of any of the following concomitant medications more than two months immediately prior or during the study:
- NSAID’s
- systemic corticosteroids
- Intake of any of the following concomitant medications with a possible effect on cognition:
- estrogen
- deprenyl
- vitamin E
- neuroleptics
- anticholinergics

Patients using stable doses of cholinesterase inhibitors were eligible, with the provision that the dose should not be changed during the study. Cholinesterase inhibitors could not be initiated during the study

- Excessive use of alcohol (> 5 units/day)
- The patient is, either alone or with the aid of a caregiver, not able to reliably take the medication.

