## Discontinuation of treatment

- The patient decides to withdraw from the study.
- Presence of serious adverse events related to the study medication.
- Questionable compliance of the patient.
- Intake of systemic corticosteroids for more than two weeks.
- The patient develops a severe and unstable disease (see also exclusion criteria).
- The diagnosis of Alzheimer’s disease is no longer plausible considering the course of the disease.
- Breaking of the medication code.

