## Side effects

The risk for gastrointestinal side effects related to the use of NSAIDs in elderly people is 20 percent. In patients of 50 years and older, using a high dosage of the NSAID indomethacin and using corticosteroids at the same time, the risk of serious gastrointestinal complications can be 10 times higher, especially during the first three months. To prevent possible gastrointestinal side effects, omeprazol (20 mg once a day) will be prescribed21.

The patient’s discomfort will be small when no inconvenient side effects occur. A (small) discomfort for the patient will be the puncture in order to get blood samples.

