## Concomitant medication

The patient’s concomitant medication will be maintained. Certain medication will lead to exclusion from the trial (see *5.3 exclusion criteria*).

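### The corticosteroid limits in Protocol Sections 5.3 and 5.4 disagree for on-study use under either reading of 5.3, and on-study NSAID use rests on the same ambiguous line

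*Protocol*

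**What the plan says.** Four places in the Protocol bear on this.

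- **Section 5.3, Exclusion criteria.** NSAIDs and systemic corticosteroids stand under the item "Intake of any of the following concomitant medications more than two months immediately prior or during the study". The preceding item (salicylates, coumarin derivatives, ACE inhibitors, loop diuretics) carries no duration at all.
- **Section 5.4, Discontinuation of treatment.** One listed reason is "Intake of systemic corticosteroids for more than two weeks". No item mentions NSAIDs.
- **Section 9.4, Side effects.** For patients aged 50 and over "using a high dosage of the NSAID indomethacin and using corticosteroids at the same time", it says that "the risk of serious gastrointestinal complications can be 10 times higher, especially during the first three months".
- **Section 9.5, Concomitant medication.** Existing medication is continued. It adds "Certain medication will lead to exclusion from the trial (see", and the reference in that parenthesis is to Section 5.3.

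**The concern.** An entry criterion and a stopping criterion may carry different durations if one governs who comes in and the other governs what happens afterwards. That separation fails here. The 5.3 item extends itself to the study period, and 9.5 treats 5.3 as the rule for concomitant medication. Two different corticosteroid rules therefore apply to the same on-study patient.

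At stake is consistent conduct across centres for a drug combination that the Protocol itself flags. Under the schedule in Appendix II, changes in concomitant medication are asked about at baseline and at weeks 4, 8, 26, 38 and 52. Two assessors who hear of the same corticosteroid course could reach opposite decisions, each with a section of the Protocol in support. The consequences are also worded differently: 9.5 speaks of exclusion from the trial, 5.4 of discontinuing treatment.

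NSAIDs raise a separate question. The test drug is an NSAID, yet on-study use of another one is covered only by the 5.3 line, and nothing in 5.4 says what happens when it occurs.

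**Working it through.** No design figure has to be reproduced. The check compares two duration rules.

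**Inputs**

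- Section 5.3: more than two months, before or during the study. Two consecutive calendar months last 59 to 62 days.
- Section 5.4: more than two weeks of systemic corticosteroids, so the criterion is met from day 15.
- Section 9.5: medication during the trial is referred to 5.3.

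**Two readings of 5.3 for on-study use**

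- Reading A: the two-month limit governs both the period before the study and the study itself.
- Reading B: the two-month limit governs only the period before the study, and any intake during the study excludes.

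**Result for an on-study corticosteroid course**

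| Length of course | 5.3, reading A | 5.3, reading B | 5.4 |
| --- | --- | --- | --- |
| 7 days | not excluded | excluded | not met |
| 14 days | not excluded | excluded | not met |
| 15 days | not excluded | excluded | met |
| 30 days | not excluded | excluded | met |
| 90 days | excluded | excluded | met |

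- Under A the sections disagree from day 15 to about two months. The band is 59 − 14 = 45 to 62 − 14 = 48 days wide.
- Under B they disagree for courses of 1 to 14 days.
- Neither reading makes them agree for every length of course. The reading changes only which durations are affected and which section is stricter.

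**A redundancy in each reading.** Under A, the on-study limb of 5.3 can never act first on a continuous course, because 5.4 is met weeks earlier. Under B, the two-week item in 5.4 can never act first, because any intake already excludes.

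**At entry.** Take a patient who has been on corticosteroids for more than two weeks but less than two months and is still taking them.

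- The pre-study limb of 5.3 is not breached under either reading.
- Under A the patient enters. Whether 5.4 is then met at baseline or about two weeks later depends on whether intake before baseline counts, which 5.4 does not say.
- Under B the patient passes the pre-study limb and breaches the on-study limb as soon as the study begins.

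**A washout meaning.** If the intention was no intake within the two months before the study, the sentence does not say so: it describes intake lasting more than two months. That meaning would remove the entry problem. It would not settle the on-study rule, which would still need reading A or B.

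**NSAIDs.** Under A, an on-study NSAID course shorter than two months meets neither section. Under B it breaches 5.3, but no listed reason in 5.4 corresponds to the breach.

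**The case against.** The strongest reply is that 5.3 and 5.4 do different jobs and that not being excluded is not the same as being permitted. Under reading A, a five-week course fails to meet an exclusion and meets a stopping criterion; both rules apply, and treatment stops. Nothing in 5.3 authorises continued use.

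Much of this stands. It defeats several stronger conclusions that a reader might draw:

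- *That the Protocol allows two months of combined exposure, covering most of the three-month period named in 9.4.* It does not. Corticosteroid use before baseline precedes study indomethacin, and on-study use beyond two weeks meets 5.4 whichever way 5.3 is read.
- *That trial patients face a tenfold risk, or that this is the gravest hazard in the Protocol.* Section 9.4 says the risk can be that high, at age 50 and over and with a high dosage. It does not call the trial regimen high dosage and does not rank the hazard. All patients are also prescribed omeprazole (Sections 9.2 and 9.4).
- *That the missing NSAID item adds to the corticosteroid risk.* The statement in 9.4 concerns corticosteroids. The NSAID gap is real but separate.
- *That NSAID use in the placebo group would materially dilute the treatment difference.* The Protocol gives no expected rate of such use. Under A the tolerated use is at most about two months of a one-year trial; under B it is none.

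The reply does not remove the conflict. It works only under reading A, and there it leaves the on-study limb of 5.3 with no function for continuous corticosteroid use. Under reading B it fails, because 5.3 rules out short courses that 5.4 tolerates. Treating 5.3 as an entry rule alone contradicts its own reference to the study period and the cross-reference in 9.5.

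**Conclusion.** The point holds as a contradiction between stated rules. For on-study systemic corticosteroids, 5.3 and 5.4 disagree for courses of 15 days to about two months under one reading and for courses of 1 to 14 days under the other. A patient on corticosteroids for between two weeks and two months can pass the pre-study condition and meet a stopping or exclusion rule at or shortly after baseline. On-study NSAID use is governed only by the ambiguous 5.3 line.

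The conclusion rests on the wording of 5.3, 5.4 and 9.5 and on counting two months as 59 to 62 days. The number of patients affected cannot be derived from the Protocol, and no effect on the sample size, the randomization or the primary analysis has been shown. The reason to correct it is consistent eligibility and stopping decisions for a combination that 9.4 flags. No view is taken on which limit is right.

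**What to change.** Reconcile Sections 5.3, 5.4, 9.4 and 9.5:

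1. Reword the 5.3 item so that the condition before baseline and the condition during the study are stated separately, and so that it is clear whether each refers to the length of intake or to a period free of the drug.
2. Make the on-study corticosteroid condition the same in 5.3 and 5.4, and state whether intake before baseline counts towards the limit in 5.4.
3. State what follows from on-study NSAID use, and let 9.5 point to the passage that governs it.

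The investigators decide the intervals and rules, taking account of the warning in 9.4. The cost is a wording amendment and possibly a few more screen failures. No visit or procedure is added.
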